**Fig. 3 Fig3:**
[figure not shown]
Trial flow & study design. General information = age, sex, weight, time when symptoms emerge, time when diagnosed, anti-SSA antibodies, abnormal Schirmer test results, decreased unstimulated salivary flow, previous systemic involvement, previous treatment with another immunosuppressant, current systemic involvement. 1st outcome = numeric analog scale (NAS) (Dryness, Pain and Fatigue). 2nd outcome = EULAR Sjogren Syndrome Patient Reported Index (ESSPRI), EULAR Sjogren Syndrome Disease Activity Index (ESSDAI), Medical Outcome Study Short From 36 Short-Form Health Survey (SF-36), Hospital Anxiety and Depression (HAD), Serum Immunoglobulin (IgG), IgA and IgM, Schirner test score and unstimulated salivary flow, salivary glands untrasounds

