#### Secondary outcome

Secondary outcomes include each items of NAS scores from week 0 to 8. These items will be measured individually at baseline, 3 times a week in week 1 to 8, once a week in week 12, 16, 20, 24. The secondary outcomes also include:EULAR Sjögren’s Syndrome Patient Reported Index (ESSPRI) [16] is a very simple index completed by patients to measure symptoms in pSS. With good construction validity, it is used as an outcome measure in clinical trials. There is a 0–10 numerical scale for each of the four domains, dryness, discomfort (including pain), global fatigue and mental fatigue, which are gathered to form the ESSPRI. For sicca features, six components were identified, which are ocular, oral, skin, nasal, tracheal and vaginal.EULAR Sjögren’s Syndrome Disease Activity Index (ESSDAI) [17, 18] is a clinical index completed by physicians to measure disease activity in patients with pSS. There are 12 organ-specific ‘domains’ contributing to disease activity. For each domain, features of disease activity are classified into three or four levels according to their severity.Schirmer test score and unstimulated salivary flow [19]: these two tests are the objective reflection to the lacrimal gland and salivary glands, the results of which can be greatly impacted by the operator. Thus, there will be a technician performing these two tests during the whole trial to maintain the homogeneity of the operation.Serum Immunoglobulin G, A, M levels [20]: Immunoglobulin G (IgG) is commonly believed in clinic a reflection of pSS symptom activities and a study shows weak associations between increasing fatigue and serum IgG, and the pro-inflammatory cytokine interleukin-17 (IL-17), were observed.Medical Outcome Study Short Form 36 Short-Form Health Survey (SF-36) [21, 22] is a self-administered questionnaire with 36 items, which assesses the concepts of physical function, role limitations due to physical problems, social function, body pain, general mental health, role limitations due to emotional problems, vitality, and general health perceptions. Note that both physical and mental component summaries can be combined. Scores range from 0 to 100, with higher scores indicating better health status [23].Salivary glands ultrasounds [24]: image of salivary glands structures. This can be quantified by a form based on different features.Hospital Anxiety and Depression (HAD) scale score [25]: A self-assessment scale which has been developed and found as a reliable instrument for detecting states of depression and anxiety in the setting of an hospital medical outpatient clinic.

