
For the secondary outcomes listed above, the measurements are conducted at baseline, in week 8, 16 and 24. Besides, the satisfaction of patients in two groups and the proportion of the subjects who identified their allocation will be measured in week 8.

Additionally, we will assess the patients’ satisfaction in week 24 by two questions. 1) “Would you like to come for more treatments or recommend it to your friends/relatives if they have similar symptoms?” The answer will be either “yes” or “no”. 2) "What is your feeling for the series of treatment?” The answers will include “excellent”, “good”, “satisfactory”, “It’s okay” and “poor”. The difference in satisfaction between two groups will be analyzed.

To evaluate the success rate of blinding, we will ask subjects in week 8 “how deep do you think the needles went into your skin?” The answer will be “deep”, “shallow” or “no penetration”. The subjects in the two groups whose answers are either “deep” or “shallow” will be considered to be blinded successfully, while “no penetration” unsuccessfully, and the proportions of them are going to be compared.

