### Statistical analysis

For data analysis, statisticians and investigators will be blinded for the patients’ allocation. Statistical analysis will be performed using SPSS Ver.20 (SPSS Inc., Chicago, IL, USA) software. Enumeration data will be described as frequency and composition ratio. Continuous data will be presented by Mean ± Standard Deviation (M ± SD) if they meet normal distribution, otherwise they will be expressed as Medians ± Interquartile Range (M ± IQR). Categorical data will be presented by frequency and percentage. The analyses of efficacy will be based on the intention-to-treat (ITT) analysis set, which was defined as patients who receive at least one treatment. Missing data for the primary outcome will be treated by multiple imputation under chained equation, with m = 50 imputations. The covariates used to generate the multiple imputed data sets are age, sex, NAS scores of DPF, ESSDAI, ESSPRI, salivary flow rate, and Schirmer test score. For comparison with the baseline, a repeated measures data analysis of variance (ANOVA) or Wilcoxon signed rank test will be used for continuous data, whereas Chi-square test or Fisher exact test will be used for categorical data. In terms of comparison between the two groups, Chi-square test or Fisher exact test will be used for primary outcomes. For secondary outcomes, the analysis of covariance (ANCOVA) will be used if the residual are normal distributed, otherwise Wilcoxon rank sum test will be applied. To access the success of blinding, the proportion of subjects who are successfully blinded will be compared by Chi-square test or Fisher exact test. And nonparametric test will be used to analyze satisfaction. *P* <0.05 with two-tailed test indicates statistical significance.

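### For any categorical item compared with baseline, the plan names chi-square or Fisher tests, which ignore that both values come from the same patients

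*Protocol article*

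**What the plan says.** The Statistical analysis section of the protocol article takes change from baseline first: "For comparison with the baseline, a repeated measures data analysis of variance (ANOVA) or Wilcoxon signed rank test will be used for continuous data". The end of that sentence adds the categorical case: "Wilcoxon signed rank test will be used for continuous data, whereas Chi-square test or Fisher exact test will be used for categorical data". The opening words about baseline govern both halves.

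The next sentence turns to the arms: "In terms of comparison between the two groups, Chi-square test or Fisher exact test will be used for primary outcomes". The blinding comparison later in the section uses the same pair of tests. Significance is judged at 0.05, two-sided ("with two-tailed test indicates statistical significance").

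The Secondary outcome section fixes the repeated measurement: "For the secondary outcomes listed above, the measurements are conducted at baseline, in week 8, 16 and 24". So every comparison with baseline sets a patient's later value against that same patient's first value. No paired test for categorical data, such as McNemar's, is named anywhere in the article.

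**The concern.** A chi-square or Fisher test of baseline against week 8 treats one arm's patients as two unrelated groups. It compares the two marginal proportions and discards the information on who changed, which is what a before-after comparison is about. When values are positively correlated within patients, the test uses too large a standard error, so its P values are too large and real changes can be missed.

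The sentence is also inconsistent within itself, because repeated measures ANOVA and the signed rank test both respect the pairing. The charitable reading, that chi-square here means McNemar's chi-square, does not fit: the test is coupled with Fisher's exact test, and the same coupling is used for the between-arm and blinding comparisons, where the samples really are independent.

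This is not a detail left to a fuller document. The article names a test, and the test does not suit the data.

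**Working it through.** **The plan's own figure.** The only computed figure is 52 per group, and this point does not depend on it. With 45% v 17.9%, two-sided 5% and 80% power, the usual formula gives 45 without and 53 with continuity correction. The pooled formula with the 2% null difference subtracted gives 52.3. Below, 52 serves only as a plausible number of pairs in one arm.

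**Why the size is wrong.** Let p0 and p1 be the proportions at baseline and follow-up, n the number of pairs, and phi the within-patient correlation of the binary values.

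- Paired variance of the difference: [p0(1−p0) + p1(1−p1) − 2·phi·√(p0(1−p0)p1(1−p1))]/n.
- The unpaired test omits the phi term. With no true change, its variance is too large by a factor 1/(1−phi).
- The true size of a nominal 5% test is then about 2·[1 − Φ(1.96/√(1−phi))]. This gives 5.0% at phi 0, 1.9% at 0.3, 0.6% at 0.5 and 0.03% at 0.7.

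**Simulation, 52 pairs in one arm.** A correlated normal variable is cut into two categories. The null is 70% at both times and the alternative is 80% falling to 62%. These proportions and the latent correlations are assumptions; the documents give neither. The latent correlation is larger than phi: at 70%/70%, latent 0.3, 0.6 and 0.8 correspond to phi of about 0.18, 0.39 and 0.58, and the formula above then gives 3.0%, 1.2% and 0.3%.

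| Latent correlation | Size, chi-square | Size, exact McNemar | Power, chi-square | Power, exact McNemar | Power, asymptotic McNemar |
|---|---|---|---|---|---|
| 0.3 | 3.1% | 2.8% | 54% | 51% | 61% |
| 0.6 | 1.3% | 2.6% | 54% | 63% | 71% |
| 0.8 | 0.3% | 2.1% | 54% | 76% | 84% |

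**A second design, 60 pairs.** The null is 50% at both times and the alternative is 50% falling to 35%, indexed by phi itself. At phi 0.3, 0.5 and 0.7, chi-square rejects a true null 2.3%, 0.7% and 0.1% of the time; asymptotic McNemar rejects 5.4%, 4.7% and 4.5%. Power of chi-square v McNemar is 37% v 51%, 34% v 64% and 30% v 91%.

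**Worked tables (hypothetical).**

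- 52 patients, 42 positive at baseline and 34 later; 9 lose the feature and 1 gains it (42 − 9 + 1 = 34). Chi-square P = 0.077, Fisher P = 0.121, exact McNemar P = 0.021.
- 60 patients, 30 positive at baseline and 20 later; 12 lose it and 2 gain it (30 − 12 + 2 = 20). Chi-square P = 0.064, Fisher P = 0.095, exact McNemar P = 0.013.

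In both tables the paired test crosses 0.05 and the unpaired tests do not.

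**The case against.** The strongest reply is that the clause may have nothing to act on. Three kinds of item look like candidates:

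- **Schirmer and salivary flow status.** The Fig. 3 legend lists "abnormal Schirmer test results, decreased unstimulated salivary flow", and a reader might infer that these yes/no items are compared before and after treatment. The legend places them under general information, with age, sex and weight. The outcomes themselves are the Schirmer score and the flow. This objection stands: they are baseline descriptors.
- **ESSDAI.** The Secondary outcome section says that within each domain "features of disease activity are classified into three or four levels according to their severity". The stated outcome is the index, and no analysis of domain levels is announced.
- **Ultrasound.** The article says that it can be quantified from its features, not that the features will be compared as categories.

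The last two remain possible targets and no more. The variables that are clearly categorical (responder status, the blinding answer and satisfaction) have no baseline value. Even so, the plan writes a rule for categorical data against baseline, so it allows for such analyses, and the rule is wrong wherever it is used.

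The second reply concerns size, and it also stands in part. The loss rests on assumed correlations. Exact McNemar is itself conservative, and at latent correlation 0.3 it has slightly less power than chi-square. It cannot be said without qualification that the planned test runs far below 5% or that it always loses power against exact McNemar.

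Third, a within-arm change from baseline is not evidence for acupuncture over sham, so no main conclusion is at risk. That is correct, and it limits the weight of the point.

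**Conclusion.** The point holds in limited form. As written, the plan assigns independent-sample tests to paired categorical data. With positive within-patient correlation the error is conservative: true size is about 3% at latent correlation 0.3 and 0.3% at 0.8, against a nominal 5%. Against exact McNemar, power is 54% v 63% at 0.6 and 54% v 76% at 0.8, with little or no loss at 0.3. These figures assume 52 pairs, a null of 70% and a change from 80% to 62%.

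A reader might go further and conclude that the trial's efficacy results are compromised, or that false positive findings will follow. The documents do not support either. The primary outcome is a responder proportion compared between independent arms, where chi-square or Fisher is right. The secondary between-arm tests, the blinding comparison, satisfaction and the sample size are all unaffected. The direction under positive correlation is missed change, not spurious change. What remains is a wrong test for secondary within-arm comparisons of whatever items are analysed as categories, and the article does not say which those are.

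**What to change.** In the sentence on comparison with baseline, replace the chi-square and Fisher clause. For items with two categories, name McNemar's test and state the version. The exact version is safe but conservative; the asymptotic or mid-P version gives up less power. For ordered levels, name a marginal homogeneity test or the signed rank test. Keep chi-square and Fisher for comparisons between the arms. It would help to list the items to which the paired categorical tests apply; if there are none, delete the clause.

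The cost is one phrase. These are standard methods, and data collection, sample size and trial conduct do not change.

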### Sample size

Sample size will be decided by the primary outcome. According to our unpublished pilot study and literature review [6], the proportions of patients with a more than 30% improvement in NAS scores in at least 2 out of 3 DPF items for acupuncture and placebo is 45% and 17.9% respectively. We use the proportion for placebo instead of the one in sham acupuncture group, because no data are available for sham acupuncture so far. A sample size of 52 for each group will be sufficient to detect a 2% null difference in proportion, with a two-sided 5% level of significance, and a power of 80%. The number of subjects is increased to 60 in each group (total of 120) when a drop-out rate of 15% is taken into consideration.

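### Before-after comparisons of categorical data are assigned independent-sample tests, and the fallback for non-normal secondary outcomes takes no baseline covariate (minor)

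*Protocol article*

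**What the plan says.** The Statistical analysis section treats two kinds of comparison in turn.

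- **Change from baseline.** "For comparison with the baseline, a repeated measures data analysis of variance (ANOVA) or Wilcoxon signed rank test will be used for continuous data". The sentence then continues: "whereas Chi-square test or Fisher exact test will be used for categorical data".
- **Between arms.** The primary outcome gets a chi-square or Fisher exact test. For secondary outcomes, "the analysis of covariance (ANCOVA) will be used if the residual are normal distributed, otherwise Wilcoxon rank sum test will be applied".

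Under Secondary outcome, the same patients are assessed repeatedly: "For the secondary outcomes listed above, the measurements are conducted at baseline, in week 8, 16 and 24". The significance rule is a single two-sided 5% level.

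The article names no paired categorical test. It does not list the ANCOVA covariates, and it does not say whether the rank-sum test is applied to post-treatment values or to changes from baseline.

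**The concern.** A comparison with baseline is a comparison of patients with themselves. The continuous half of the sentence respects this, since repeated-measures ANOVA and the signed-rank test are both paired methods. The categorical half does not: chi-square and Fisher tests treat the baseline and follow-up readings as two separate groups of people. When readings on the same person are positively correlated, these tests overstate the variance of the change. P-values come out too large and real changes are missed.

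The between-arm fallback raises a milder issue. ANCOVA is normally chosen to adjust for baseline. If the residuals look non-normal, the plan moves to a test that accepts no covariate. Skewed or bounded measures such as ESSDAI, Schirmer score, salivary flow or the ultrasound score could plausibly trigger the switch, and they would then lose the precision that adjustment gives.

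**Working it through.** **Stated figure.** This point disputes no number in the article. The 52 per group, used below as the arm size, reproduces from 45% against 17.9%, a 2% null difference, two-sided 5% and 80% power:

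- mean proportion = (0.45 + 0.179)/2 = 0.3145
- n = [1.960·√(2·0.3145·0.6855) + 0.842·√(0.45·0.55 + 0.179·0.821)]² / (0.271 − 0.02)² = 52.3

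**Which comparison the sentence covers.** It opens with comparison with baseline and uses the signed-rank test, which needs pairs. The next sentence turns to comparison between the two groups. The chi-square or Fisher clause therefore concerns before-after data, not a between-arm table.

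**Part 1: paired categorical data**

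Inputs: n = 60 (one arm as randomised, from Sample size). Assumed, because the documents give neither: 70% abnormal before and 50% after, and latent within-patient correlation 0.3, 0.5 or 0.7.

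The variance of the change is [p₁q₁ + p₂q₂ − 2φ√(p₁q₁p₂q₂)]/n, where φ is the correlation of the two binary readings. The chi-square test omits the φ term. With equal rates its true size is about 2[1 − Φ(1.96/√(1 − φ))]. At a 50% rate, φ = (2/π)·arcsin(latent correlation):

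| Latent correlation | φ | 1.96/√(1 − φ) | True size |
|---|---|---|---|
| 0.3 | 0.194 | 2.18 | 2.9% |
| 0.5 | 0.333 | 2.40 | 1.6% |
| 0.7 | 0.494 | 2.76 | 0.6% |

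Simulation agrees: about 3%, under 2% and 0.7% for chi-square, against about 5% for McNemar's test.

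One expected table shows the mechanism. At latent correlation 0.5, a change from 70% to 50% gives discordant shares of 27.8% and 7.8%, or 16.7 and 4.7 of 60 patients.

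- McNemar: z = (16.7 − 4.7)/√(16.7 + 4.7) = 12.0/4.63 = 2.59
- Chi-square: z = 0.20/√(0.60·0.40·2/60) = 0.20/0.0894 = 2.24

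Simulated power, 70% to 50%:

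| Latent correlation | Chi-square | McNemar | Exact McNemar |
|---|---|---|---|
| 0.3 | 63% | 71% | 61% |
| 0.5 | 64% | 78% | 70% |
| 0.7 | 66% | 87% | 81% |

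Other rates give the same direction. For 60% to 40% at φ = 0.5, power is 65% (chi-square), 54% (Fisher) and 88% (McNemar). Size at 50%/50% is 0.7%, 0.3% and 4.7%.

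**Part 2: rank-sum fallback**

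Inputs: 52 per arm (Sample size). Assumed: lognormal outcome with log-SD 0.7, treatment shift of 0.5 SD on the log scale, baseline-outcome correlation 0.3 to 0.7; 2,000 runs per power figure, so a simulation error of about √(0.7·0.3/2000) = 1 percentage point.

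| Correlation | Rank-sum, post values | Rank-sum, change | Rank ANCOVA |
|---|---|---|---|
| 0.3 | 68% | 54% | 72% |
| 0.5 | 71% | 70% | 82% |
| 0.7 | 67% | 88% | 91% |

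A separate run gave 68-70% for rank-sum on post values and 71-92% for rank ANCOVA. With no treatment effect, the rejection rates of these two tests were 4.4-5.3% and 4.6-5.5%.

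**The case against.** The strongest reply is that Part 1 has no named target. The primary responder status already contains the baseline and is compared between arms, where chi-square or Fisher is suitable. Satisfaction and the blinding question are asked only after treatment. The remaining secondary outcomes are described as indices, scores, flows or levels. The 70% to 50% example is therefore hypothetical. The error is also conservative under positive correlation, and it sits in within-arm tests, which carry no randomised contrast. All of this stands and sets the severity. It does not rescue the sentence, which names the wrong test for whatever graded or dichotomised measure is compared with baseline.

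On Part 2, a fallback stated in advance is conventional, and its type I error is sound. That the ANCOVA covariate is baseline is inferred. If the rank-sum test were run on changes, part of the baseline information would return, and at correlation 0.7 the gap to rank ANCOVA nearly closes (88% against 91%). At 0.3, however, it widens (54% against 72%).

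Three stronger readings are tempting and not supported:

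- **The secondary tests in general discard within-patient information.** They do not: continuous before-after data get paired methods, and ANCOVA is the first choice between arms.
- **Dropping baseline costs ρ² of the patients, so 25% to 49% at correlations of 0.5 to 0.7.** That rule compares adjusted with unadjusted means in a linear model. The fallback is a rank test used when residuals are not normal. Under strong skew (log-SD 1.3), raw-scale ANCOVA with robust errors reaches only 43-57% power against about 70% for rank-sum.
- **Drop-outs are lost from the secondary analyses, or a longitudinal model is required.** The article specifies imputation for the primary outcome and is silent on the rest. It does not state a complete-case analysis, and an article may leave such detail to the full protocol or analysis plan.

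**Conclusion.** The point holds in two limited parts, and its severity is minor.

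1. The stated test for categorical change from baseline is wrong for paired data. Under the assumed latent correlations of 0.3 to 0.7, its real size is about 3% to 0.7% and it gives up roughly 8 to 21 points of power against McNemar's test (71 − 63 and 87 − 66). The direction depends on positive within-patient correlation, which is plausible but not documented. Exact McNemar is itself conservative and gains over chi-square only from a correlation of about 0.5 upwards.
2. The rank-sum fallback is valid but imprecise. Compared with rank-sum on post-treatment values, a baseline-adjusted rank analysis gains from a few points of power at correlation 0.3 to more than 20 at 0.7, in the skewed scenario assumed here.

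Neither part touches the primary between-arm comparison.

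**What to change.** In Statistical analysis:

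- Replace chi-square or Fisher with McNemar's test, or another paired categorical method, for any before-after categorical comparison. Label within-arm tests as descriptive. Keep chi-square or Fisher for between-arm categorical comparisons.
- Replace the rank-sum fallback with a baseline-adjusted one, such as rank ANCOVA or ANCOVA on a transformed scale, and name baseline as the covariate.

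The cost is a few lines of wording and standard software, with no extra data or patients. The one drawback is that rank ANCOVA gives its estimate on the rank scale, which is harder to interpret clinically.

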#### Primary outcome

The numeric analog scale (NAS) [14] scores of DPF (0 = the best, 10 = the severest) will be measured at the baseline, three times a week in week 1 to 8, and once a week in week 12, 16, 20, and 24. By the comparison of the average scores of week 2 to 8 with those of the baseline of the two arms, the proportions of the subjects in two groups that have 30% or greater reductions in NAS scores in at least 2 out of 3 DPF items, will be the primary outcome.

Subjects will be asked to provide every NAS score based on the overall situation of the past 24 h [15] rather than a point of time. And we will collect NAS scores 3 times a week in week 1 to 8 (24 times in total).

The mentioned outcome measurements will be assessed at the marked time points respectively (Fig. 3).

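### Primary comparison: replace the unadjusted chi-square or Fisher test on 50 imputed data sets with a Rubin-pooled, baseline-adjusted estimate and confidence interval (a gain in precision and reporting, not a type I error correction)

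*Protocol article*

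**What the plan says.** The Primary outcome section defines a binary endpoint: "the proportions of the subjects in two groups that have 30% or greater reductions in NAS scores in at least 2 out of 3 DPF". Response is judged against each subject's own starting score: "By the comparison of the average scores of week 2 to 8 with those of the baseline of the two arms".

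The Statistical analysis section sets the missing-data method: "Missing data for the primary outcome will be treated by multiple imputation under chained equation, with m = 50 imputations". It lists the imputation variables: "The covariates used to generate the multiple imputed data sets are age, sex, NAS scores of DPF, ESSDAI, ESSPRI, salivary flow rate", followed by the Schirmer score. Arm is not in the list. The test is then fixed: "In terms of comparison between the two groups, Chi-square test or Fisher exact test will be used for primary outcomes". No covariate, effect measure or interval accompanies it. The next sentence treats the secondary outcomes differently: "For secondary outcomes, the analysis of covariance (ANCOVA) will be used if the residual are normal distributed", with a rank test otherwise. The article does not name the ANCOVA covariates.

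The Sample size section works with two proportions, "for acupuncture and placebo is 45% and 17.9% respectively".

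**The concern.** Imputation with m = 50 produces 50 completed tables, whereas chi-square and Fisher tests are each made for one table. Rubin's rules combine an estimate and its standard error. Fisher's test supplies neither, and the chi-square supplies only a statistic. The primary result would then be at best a p-value, with no statement of how large the difference is or how precisely it is known.

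The test also leaves the measured baseline scores out of the between-arm comparison. The endpoint is a percentage reduction, and the inclusion criteria set no minimum score, so baseline level may well predict response. If it does, adjustment would gain some power from data already collected.

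**Working it through.** **1. The plan's own figure.** Inputs from the Sample size section: 45% and 17.9%, null difference 2%, two-sided 5%, power 80%.

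- Mean proportion = (0.45 + 0.179)/2 = 0.3145.
- n = [1.960 × √(2 × 0.3145 × 0.6855) + 0.8416 × √(0.45 × 0.55 + 0.179 × 0.821)]² / (0.271 - 0.02)² = 52.3 per group.
- Exact Fisher power at 52 per group is 80.4%.

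The stated 52 is reproduced to within one patient, and the fix does not change it.

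**2. Does the way of combining 50 results matter?** Simulation of 3,000 trials, 60 per arm. Assumptions: 9 of 60 outcomes (15%) missing completely at random in each arm, imputed within arm, m = 50.

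| | 45% vs 17.9% | 17.9% in both arms |
|---|---|---|
| The 50 chi-square tests do not all agree on p < 0.05 | 34.5% of trials | 30.2% of trials |
| D2-pooled chi-square rejects | 0.857 | 0.045 |
| Rubin-pooled risk difference rejects | 0.861 | 0.048 |

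So pooling is needed, and a pooled chi-square is available and sound. The pooled risk difference does as well and also gives an estimate with an interval.

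**3. What does baseline adjustment gain?** Simulation of 2,000 trials per setting with complete data and one standardised baseline covariate. The prognostic strength of baseline is not in the document, so the odds ratio (OR) per SD is an assumption, shown as a range.

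| OR per SD | 60 per arm: chi-square / adjusted | 51 per arm: chi-square / adjusted |
|---|---|---|
| 1.0 | 0.910 / 0.902 | 0.863 / 0.857 |
| 1.5 | 0.920 / 0.922 | 0.846 / 0.849 |
| 2.2 | 0.909 / 0.933 | 0.859 / 0.890 |
| 3.3 | 0.919 / 0.955 | 0.872 / 0.919 |

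The change runs from about -1 to +5 points. Type I error was 4.2% to 5.3% unadjusted and 3.9% to 4.9% adjusted (Monte Carlo error about 0.5 points).

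**4. How many covariates can the model carry?** Expected responders are 60 × 0.45 + 60 × 0.179 = 27 + 10.7, about 38. Arm plus three items gives 38/4, about 9 per parameter. Arm plus the mean of the three items gives 38/2 = 19.

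**5. Shortcuts that the article does not propose.** Suppose the test were run on averaged counts, or on a single completed data set, with 15% missing. The test assumes a variance of pq/60 per arm (p the response rate, q = 1 - p).

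- Imputed within arm, averaged counts: the true variance is pq/51. The ratio is 60/51 = 1.18, and 1.96/√1.18 corresponds to a level of about 7.1%.
- Imputed within arm, one data set: add 0.15² × (1/51 + 1/9) × pq. The ratio is 60 × (0.0196 + 0.0029) = 1.35, and the level is about 9.2%.
- Arm left out of the imputation, as listed: the ratio is 51/60 = 0.85 for averaged counts (level about 3.4%) and (51 + 9)/60 = 1 for one data set (level about 5%). Simulation gave 3.5% and 5.3%.

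The inflation therefore needs both an unstated shortcut and an imputation model that contains arm.

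**The case against.** The strongest reply has three parts.

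- The named test can be done validly: chi-square statistics pool by D2 at almost no loss of power, and with about 38 expected responders the Fisher option is unlikely to be needed. This stands. D2 still yields no effect size or interval.
- How results are combined and which effect measure is reported are details that an article may leave to a full analysis plan. This also stands, and silence on those details is not the point made here. The point concerns the test that the article does fix, which would have to be extended or replaced to give a pooled estimate.
- Baseline is already used through the definition of response, and an unadjusted comparison in a 1:1 randomised trial is valid and matches the two-proportion sample size. This is correct. Adjustment is a choice made for precision.

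A reader might go further and infer that the primary analysis cannot be carried out validly, or that its type I error is inflated to between 7% and 10%. The document supports neither. It nowhere says that one completed data set or averaged counts would be tested, and the inflation disappears or reverses under the imputation variables as listed.

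**Conclusion.** The point holds as a modest, inexpensive improvement. An unadjusted chi-square or Fisher test is a weak partner for 50 imputations: one option has no standard pooled form, the other pools only to a p-value, and neither uses the baseline scores to gain precision. Nothing here shows an error in the significance level.

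The expected power gain is roughly 0 to 5 points. It is nil or very slightly negative if baseline does not predict response, and nears 5 only if it predicts strongly (OR per SD of about 3.3). That strength is assumed. The surer gain is a primary effect estimate with a confidence interval. The pooling results assume 15% wholly missing outcomes, missing at random, with imputation within arm. The 15% is the drop-out allowance for a 24-week trial, and some subjects who leave will have partial week 2 to 8 data.

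**What to change.** Before unblinding, replace the primary-test sentence with the following plan.

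1. In each of the 50 data sets, fit a logistic regression of responder status on arm and a small pre-specified baseline set: the mean of the three baseline NAS items or, at most, the three items themselves.
2. Pool the log odds ratio for arm by Rubin's rules, and take the primary p-value from it.
3. Standardise each fitted model to the trial population and report the pooled risk difference with 95% CI, on the scale of the proportions in the Sample size section. State that the p-value in step 2 decides the primary result if the two disagree at the margin.
4. Keep the unadjusted chi-square or Fisher test on observed cases as a sensitivity analysis.

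Pooling a model that contains arm presumes that arm is also in the imputation model. The listed variables do not include it, so that list should be settled at the same time.

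If adjustment is not wanted, a Rubin-pooled unadjusted risk difference with 95% CI meets the reporting need. The cost is a few sentences and slight extra programming. The one drawback is that logistic regression gives a conditional odds ratio, which is why step 3 is needed. The sample size is unchanged.
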